#### Data collection

During the baseline and follow up period, the *patient data *were collected in two ways. To measure AEs and preventive care the research assistants read the patient files and observed the patients during a weekly visit. To measure the utilization of preventive care, wards were visited three times by research assistants. At each visit they observed a sample of at least five patients and nurses during their daily activities for five hours.

All nurses were asked to fill in a questionnaire at the start of the baseline period and the follow-up period.

#### Statistics

Power calculation was based on the primary outcome, with a two-sided alpha of 0.05 and 80% power for the analysis of both the hospital and the nursing homes data.

As randomisation was on ward level, a ward was considered to be a cluster. To account for these clusters an intra class correlation coefficient of 0.01 was used in the calculation.

In hospitals, the incidence of pressure ulcers (10%) will be the highest contributor to our combined AE measure. The incidence of urinary tract infection and falls in the same patients is unknown. Therefore we assumed that the count of these three AEs will be 12% (an additional 1% for falls and 1% for urinary tract infections). We aimed to achieve a reduction of 50% as studies on the prevention of pressure ulcers have shown this is attainable [45,46]. To detect a decrease in AEs (from 12% – 6%) 1250 patients had to be included in each hospital group.

In the nursing homes, the incidence of falls will be the highest (60%). We assume that the additional contribution of pressure ulcers and urinary tract infection to AEs will be negligible. We aimed to achieve a reduction of 60% as a study on the prevention of falls showed this was attainable [47]. Therefore this study wanted to achieve a reduction of AEs from 60 – 36%. To detect this decrease in the nursing homes, 100 patients had to be included in each group.

The results will be analysed separately for hospitals and nursing homes, as patient characteristics, length of stay and nurse characteristics differ between hospitals and nursing homes.

The difference in incidence of AEs between the intervention and the control group during the follow up period will be analysed using a random effects Poisson regression analysis, including the following covariates: ward (random effect), institution and the baseline results of the ward.

The secondary outcomes will be evaluated in a similar way, using linear and logistic random effect models.

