### Phase 2: cluster randomised clinical trial to evaluate the patient safety program

#### Study design and setting

A cluster randomised trial was conducted between September 2006 and November 2008 in the Netherlands. Hospitals and nursing homes were asked to participate with two or four, more or less comparable, wards. The hospital wards (n = 10) were internal medicine wards (n = 4) and surgical wards (n = 6) from four hospitals. The nursing home wards (n = 10) were wards with patients with physical impairments (no dementia)(n = 7) or rehabilitation wards (n = 3) from six nursing homes. The randomisation of the wards was stratified for centre and type of ward (Figure 1) and took place prior to baseline data collection.

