**Figure 1 F1:**
[figure not shown]
**Randomisation**.

Baseline data collection took place from September through November 2006. Subsequently, the patient safety program was implemented on the intervention wards: five hospital wards and five nursing home wards from December 2006 – February 2008. The wards of the control group continued care as usual. The follow-up period was nine months and continued until the end of November 2008.

The Medical Ethics Committee of district Arnhem – Nijmegen assessed the study and waived the need for complete evaluation of the study.

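### The hospital sample size of 1250 per group allows for the ICC but not for having only ten wards; on 8 ward-level degrees of freedom its power is about 70%, not 80%

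*Protocol article*

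**What the plan says.** All references are to the protocol article, Phase 2.

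- **Error rates.** The Statistics section opens: "Power calculation was based on the primary outcome, with a two-sided alpha of 0.05 and 80% power for the analysis of both the hospital". The same error rates apply to nursing homes.
- **Clustering.** "As randomisation was on ward level, a ward was considered to be a cluster", and "To account for these clusters an intra class correlation coefficient of 0.01 was used in the calculation". No source is given for the ICC.
- **Effect and size.** "To detect a decrease in AEs (from 12% – 6%) 1250 patients had to be included in each hospital group".
- **Number of wards.** Study design and setting reports: "The hospital wards (n = 10) were internal medicine wards (n = 4) and surgical wards (n = 6) from four hospitals". The program was implemented on "five hospital wards and five nursing home wards from December 2006 – February 2008", which leaves five hospital wards per arm.
- **Allocation.** "The randomisation of the wards was stratified for centre and type of ward".
- **Analysis.** The Statistics section plans a Poisson regression with a random ward effect, adjusted for institution and for the ward's baseline results, run separately for hospitals and nursing homes.

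The Discussion says that correlation within wards was dealt with by putting an intracluster correlation into the power calculation. Neither section mentions an allowance for the small number of wards, and the formula is not printed.

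**The concern.** A design effect inflates the variance for a known ICC. It does not account for the between-ward variance having to be estimated, here from ten hospital wards. The treatment contrast is a comparison between wards, so its test statistic has few degrees of freedom and a critical value well above 1.96. If 1250 was derived with normal quantiles, the stated 80% power and the stated two-sided 0.05 cannot both hold for an unadjusted comparison of five wards with five.

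At stake is how a null hospital result is read. The stated design implies a 20% chance of missing a true halving of adverse events. On 8 df that chance is about 30%. If the analysis instead keeps a normal critical value, the cost moves to the type I error.

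**Working it through.** **Inputs.** p1 = 0.12, p2 = 0.06, two-sided alpha 0.05, power 80%, ICC 0.01 and 1250 per group (Statistics); five wards per arm and four hospitals (Study design and setting). Equal ward sizes are assumed, so m = 1250/5 = 250.

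**1. Reproducing 1250.**
- Individual-level size: n = [1.96·√(2·0.09·0.91) + 0.8416·√(0.12·0.88 + 0.06·0.94)]² / 0.06² = 355.9, so 356 per group.
- Design effect: 1 + (250 − 1)·0.01 = 3.49.
- 356 × 3.49 = 1242. The version for a fixed number of clusters, 356·(1 − 0.01)/(1 − 356·0.01/5), gives 1224.

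Both are close to 1250. A t-based calculation on 8 df with five wards per arm would need about 5870 per arm. Normal quantiles are therefore the natural explanation of 1250.

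**2. Power at 1250, binomial variance.**
- SE = √[3.49/1250 × (0.1056 + 0.0564)] = 0.0213.
- Noncentrality = 0.06/SE = 2.82.
- Degrees of freedom: 10 wards − 2 arms = 8. Deducting institution (4 − 1 = 3) and ward baseline (1) leaves 4.

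| Reference | Critical value | Power |
|---|---|---|
| Normal | 1.96 | 80.5% |
| t, 8 df, no covariates | 2.306 | 69.6% |
| t, 4 df, covariates remove no between-ward variance | 2.776 | 57.0% |

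**3. Simulation.** 200,000 beta-binomial trials with five wards of 250 per arm and ICC 0.01, comparing ward proportions:

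| Critical value | Power | Type I error |
|---|---|---|
| t, 8 df | 70.6% | 4.9% |
| Normal, 1.96 | 80.5% | 8.5% |

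**4. What the covariates would have to achieve.** On 4 df, 80% power needs a noncentrality of 3.76. The variance of the contrast must fall by 1 − (2.82/3.76)² ≈ 0.44. The design effect becomes 3.49 × 0.56 ≈ 1.96, so the residual ICC is 0.96/249 ≈ 0.004. At exactly 0.004 the power is 79.4%.

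**5. Poisson variance.** Replacing 0.162 by 0.12 + 0.06 = 0.18 and keeping the design effect of 3.49 gives a noncentrality of 2.68. Power is 76% (normal), 65% (8 df) and 53% (4 df).

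**6. Sensitivity to the ICC** (binomial variance, 1250 per group):

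| ICC | Normal | t, 8 df | t, 4 df |
|---|---|---|---|
| 0.005 | 94% | 87% | 75% |
| 0.01 | 81% | 70% | 57% |
| 0.02 | 58% | 47% | 38% |

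**7. More patients per ward.** The effective size per arm is 1250/3.49 = 358. With five wards at ICC 0.01 it cannot exceed 5/0.01 = 500, however many patients are enrolled.

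**The case against.** **The arithmetic is not wrong.** This stands. 1250 follows from the stated inputs by a standard route, and a reader should not infer a calculation slip. What is missing is an allowance for few clusters. The route is itself inferred, because the article prints no formula.

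**The test and its degrees of freedom are not stated.** A condensed article may leave these to a fuller document, so 8 and 4 df are assumptions. This does not rescue the 80%. A t-type test gives the lower power. A normal-type test keeps 80% only with a type I error near 8.5% in the simulated ward-level comparison, which breaks the stated 0.05.

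**Stratification and adjustment may recover power.** This is the strongest point, and it limits the claim. Centre and ward type are stratification factors, and institution and ward baseline are in the model; any of these could remove between-ward variance. A reader might infer that power is 70% at most, or that it is really 57%. The documents support neither: 57% charges the covariates for four degrees of freedom and credits them with nothing. Equally, they do not support assuming that the loss is made good, because the sample size calculation claims no covariate gain. The 8 df figure cannot be combined with such a gain, since 8 df is the count with no covariates fitted.

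**The 70% does not describe the planned Poisson model.** This is fair, and is why the Poisson figures belong beside it.

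**The trial has been conducted, and its result will be read from the estimate and interval.** That lowers the stakes. The stated power remains inaccurate, though, and the choice of reference distribution also determines whether the interval has its nominal coverage.

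**Conclusion.** The point holds. On the article's own inputs, 1250 per hospital group with five wards per arm does not give 80% power at two-sided 0.05. Without covariates it gives about 70% (8 df), a shortfall of about ten percentage points. With institution and ward baseline fitted, power is 57% if they explain nothing and about 80% only if the residual ICC falls to about 0.004. With Poisson variance, 65% and 53% replace 70% and 57%.

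These figures assume equal wards of 250, all 1250 patients per group counting in the follow-up comparison, an ICC of 0.01, a ward-level t reference, and a normal approximation behind the stated size. The ICC matters most: on 8 df, power is 87% at 0.005 and 47% at 0.02.

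A reader might also infer that the trial needed more patients on the same wards. The calculation does not support that remedy: the present number already yields 358 of at most 500 effective patients per arm. On 4 df without covariate gain, even unlimited enrolment would give only about 71%.

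**What to change.** 1. Restate hospital power for 1250 per group as about 70%, with its assumptions: t reference on 8 df, ICC 0.01, binomial variance, no covariate gain.
2. Beside it, give the Poisson-variance figures (about 65% on 8 df and 53% on 4 df) and a sensitivity line for ICC 0.005 to 0.02: 87% to 47% on 8 df, and 75% to 38% on 4 df.
3. State that the hospital effect is tested against a small-cluster t reference, so that alpha stays at 0.05.

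Enrolment does not change. The cost is a less favourable stated power and, under item 3, a wider interval for the hospital effect than a normal reference would give.

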#### Outcome measures

The primary outcome measure was the incidence of AEs (sum of the incidence of pressure ulcers, urinary tract infections and falls).

A *pressure ulcer *is an area of localised damage to the skin and underlying tissue caused by a combination of pressure and shear[21]. Pressure ulcers are classified in four grades according to the guidelines [19,21,40]. Pressure ulcers were considered present if a patient developed a PU grade 2 or worse. If a patient had a PU grade two or worse at the first visit, that PU lesion was excluded from the registration of PUs until the PU healed. Patients with an already present PU grade two or worse were only registered if they developed additional PU lesions.

A *urinary tract infection *is bacteriuria with clinical symptoms as: frequent urinating, pain while urinating, abdominal pain, fever and delirium, urinary incontinence [18,24]. During this study we defined a urinary tract infection as present if it was diagnosed by a medical doctor. Patients were excluded from the registration of urinary tract infection for a period of three weeks if they had a urinary tract infection until the infection was cured.

A *fall *is an unexpected event in which the participant comes to rest on the ground, floor, or lower level [20,41]. In this study the falls were measured by examining the patient files, assuming that if a patient fell it was reported in his or her file.

The secondary outcome measures were 1) the percentage of patients that received preventive care and 2) the knowledge of nurses regarding the three topics.

*Prevention *is important in patients at risk for one of the AEs. Preventive measurements were considered present when the care was performed according to the guideline.

The risk of *pressure ulcers *was measured with the PrePURSE [27] and the Braden scale [42] in hospitals and nursing homes, respectively. Next preventive care was measured: position while lying or sitting; if patients' heels were lifted; use of pressure-reducing material or alternating pressure material in bed or chair; presence of a repositioning scheme.

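### The sample sizes were not computed for the planned Poisson analysis of summed AEs; nursing-home power at 100 per group is about 60–65% or about 95%, depending on what 60% and 36% measure

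*Protocol article*

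**What the plan says.** Under Outcome measures, the protocol article states: "The primary outcome measure was the incidence of AEs (sum of the incidence of pressure ulcers, urinary tract infections and falls". The Statistics section analyses this outcome by random effects Poisson regression, with ward as a random effect and with institution and the ward's baseline results as covariates.

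The same section bases power on the primary outcome, "with a two-sided alpha of 0.05 and 80% power for the analysis of both the hospital and the nursing homes data", and says that "an intra class correlation coefficient of 0.01 was used in the calculation". For hospitals it adds 10%, 1% and 1%: "we assumed that the count of these three AEs will be 12" per cent, to be halved to 6%, with 1250 patients per group. For nursing homes it says "In the nursing homes, the incidence of falls will be the highest (60" per cent), treats the other two AEs as negligible, speaks of a 60% reduction, gives the target as 60 to 36%, and concludes: "To detect this decrease in the nursing homes, 100 patients had to be included in each group".

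The article names no formula. It does not say whether the 60% is falls per resident or the share of residents who fall.

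**The concern.** A sample size holds for the outcome and variance used to compute it. A yes/no outcome with probability p has variance p(1−p). A Poisson count with mean λ has variance λ, and more if some patients have repeated events. At 12% the two are close (0.106 against 0.12). At 60% they differ 2.5-fold (0.24 against 0.60). A formula for proportions therefore does little harm in hospitals but can badly overstate power in nursing homes if the analysis counts events.

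At stake is the 80% power claim. If true power is near 60%, a null nursing-home result says much less than a reader would conclude from the stated figure.

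**Working it through.** **Inputs from the article.** Two-sided alpha 0.05 and 80% power (z = 1.96 and 0.8416; squared sum 7.849); ICC 0.01; intervention wards are "five hospital wards and five nursing home wards" out of ten in each setting, so five per arm; 1250 and 100 patients per group. *Assumptions:* equal ward sizes (250 and 20) and a normal reference distribution. The design effect is 1 + (m − 1) × 0.01, which is 3.49 in hospitals and 1.19 in nursing homes.

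**1. Hospital figure as proportions.** n₀ = [1.96√(2 × 0.09 × 0.91) + 0.8416√(0.1056 + 0.0564)]² / 0.06² = 356. Then 356 × 3.49 = 1,242. With five wards per arm held fixed, n₀(1 − ρ)/(1 − n₀ρ/5) = 1,224. The stated 1250 is recovered.

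**2. Hospital figure as Poisson.** On the rate difference, n₀ = 7.849 × 0.18/0.06² = 393, and × 3.49 = 1,372. On the log rate ratio it is 409 × 3.49 = 1,427. Neither gives 1250.

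**3. Nursing-home figure as proportions.** n₀ = [1.96√(2 × 0.48 × 0.52) + 0.8416√(0.24 + 0.2304)]² / 0.24² = 67. Then 67 × 1.19 = 80, or 77 with five wards fixed (76 before rounding n₀ up). With continuity correction, 75 × 1.19 = 89, or 87. The stated 100 is higher, and would have 88–89% power for proportions.

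**4. Nursing-home figure as Poisson.**
- Difference scale: n₀ = 7.849 × 0.96/0.24² = 131, giving 156 at design effect 1.19 or 176 with five wards fixed.
- Log scale: n₀ = 134, giving 160 or 181.
- Square-root scale: n₀ = 129, giving 154 or 172.

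The stated 100 is well below all of these.

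**5. Nursing-home power at 100 per group, percentages read as events per patient (0.60 and 0.36).**

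| Variance assumed | Power |
|---|---|
| Poisson × 1.19, difference scale: SE = √(1.19 × 0.96/100) = 0.107; z = 2.25 | 61% |
| Same, log scale | 60% |
| Poisson within wards, between-ward variance 0.01 × p(1−p): SE = √(0.96/100 + 0.01 × 0.4704/5) = 0.1027; z = 2.34 | 65% (63% on log scale) |
| No clustering at all | 68–69% |
| λ + 0.5λ², × 1.19: SE = √(1.19 × 1.2048/100) = 0.120; z = 2.00 | 52% |
| λ + λ², × 1.19: SE = √(1.19 × 1.4496/100) = 0.131; z = 1.83 | 45% |

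Overdispersion of 0.5 and 1 is an assumption; the article gives no value. The fourth row is a ceiling on what removing ward-level variation could achieve, and it is still below 80%.

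**6. Nursing-home power, percentages read as shares with at least one AE.** Under a Poisson distribution the means are −ln(0.40) = 0.916 and −ln(0.64) = 0.446. Power at design effect 1.19 is 95–96%.

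**7. Hospital power at 1250, read as events per patient (0.12 and 0.06).** SE = √(3.49 × 0.18/1250) = 0.0224, z = 2.68, power 76% (75% on the log scale). With between-ward variance 0.01 × p(1−p): SE = √(0.18/1250 + 0.01 × 0.162/5) = 0.0216, z = 2.77, power 79%.

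**8. Stated reduction.** (60 − 36)/60 = 40%. A 60% reduction from 60% would be 24%. At 0.60 against 0.24 events per patient, Poisson power at 100 per group would be 94–95%.

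**The case against.** The strongest reply is that nothing ties the nursing-home 60% to events per resident. The word count is attached only to the hospital 12%, and Table 2 of the article words its incidence indicators for pressure ulcers and urinary tract infections as percentages of patients developing the event. If 60% and 36% are shares of residents, the planned Poisson analysis has more than the stated power. This stands. A reader might infer that the nursing-home comparison simply has 61% power, and the documents do not support that as a fact of the design.

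A reader might also infer that both sample sizes were visibly computed as comparisons of proportions. Only the hospital figure shows this. The nursing-home 100 would need an unstated extra, such as 20% loss to follow-up (80/0.8 = 100) or wards of about 50 (67 × 1.49 = 99.8).

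The conflict over the size of the reduction also stands: until it is settled, even the events-per-patient reading does not fix one power figure. The hospital gap is slight.

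It can further be said that a condensed article may leave the formula to the full protocol. That excuses the missing formula. It does not excuse an outcome, model, planning figures and group sizes that are all printed and do not fit together.

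**Conclusion.** The point holds as a mismatch between the power calculation and the planned analysis. The hospital 1250 rests on binomial variance, and the nursing-home 100 fits neither the binomial nor the Poisson calculation.

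The reading most consistent with the article is events per patient: the outcome is a sum, the hospital figure is built by addition and called a count, and the model is Poisson. On that reading, with an effect of 60 to 36%, nursing-home power is about 60–65%, and about 45–52% with patient overdispersion of 0.5–1. On the share reading it is about 95%. The stated 80% follows from neither. Hospital power on the events reading is about 75–79%, a small shortfall.

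These figures assume equal ward sizes, ICC 0.01 and a normal approximation. They do not show that the Poisson model is invalid or its estimate biased; what is in doubt is the power claim.

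**What to change.** 1. State whether 60%/36% and 12%/6% are events per patient or shares of patients with at least one AE.
2. Reconcile the stated 60% reduction with 60 to 36%.
3. Recompute power for the planned model, using Poisson variance, a stated range of overdispersion and the ward clustering.
4. Restate the power at 100 and 1250 per group, or the rate ratio detectable with 80% power. On the events-per-patient reading, without overdispersion and with design effects 1.19 and 3.49, that ratio is about 0.51 in nursing homes: difference 0.294, SE = √(1.19 × 0.906/100) = 0.104, z = 2.83. In hospitals it is about 0.47–0.48.

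The summed primary outcome and the Poisson model stay. Redefining the outcome as patients with at least one AE would also align the two, but it discards repeat events and changes the primary question, so it is a real trade-off and not a wording change.

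The cost is a short recalculation and a few rewritten sentences in the Statistics section. No extra patients are needed.

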The implementation of the digital registration and feedback system was even more complex. Currently, registration of patient care in a computer is not a standard procedure in the Netherlands. The nursing files are still mainly paper files. Moreover, not all nurses of the participating wards were used to working with a computer and on some wards the nurses did not even have access to a computer or the internet. We explored these barriers in a very early stage of the implementation process. This allowed us to remove the practical barriers, i.e. attaining access to a computer and the internet, and organise training programs for nurses to improve computer skills. Also, it gave the wards the opportunity to adopt the idea of registration of patient care on a computer. By the time they had to work with the digital registration and feedback system they were already used to the idea of using a computer.

Unfortunately it was not possible to prevent double registration of patient data: nurses had to write patient files and also register the patient daily care in the computer. This is only worthwhile when the digital program is of benefit to the nurses. Therefore, nurses were trained and encouraged to use the feedback provided by the digital program to evaluate and adjust daily care.

The final challenge we want to discuss is the design of the cluster randomised trial. Cluster randomised trials are more complex to perform, as they require more participants [48], due to the correlation between individuals in the same ward. In this study we took this into account by including an intra cluster correlation coefficient in the power calculation. As a result we had to include many hospital patients: 1250 in each group. To include and follow up that many patients in such a short time is ambitious, but we are convinced that it is achievable. Also, analyses of cluster randomised trials are complex. For analysing the effect of an intervention, a regression analysis including covariates should be used to account for the influence of the wards. Therefore this study will consider the following covariates: ward (random effect), institution and the baseline results of the ward.

Dissemination of the results of this study is planned for 2009.

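### With ten wards per setting, the primary model leaves 4 (hospitals) or 2 (nursing homes) ward-level degrees of freedom, so its usual large-sample tests over-reject in hospitals

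*Protocol article*

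**What the plan says.** Protocol article, Statistics: the two settings are analysed separately, and follow-up incidence of adverse events is compared between arms "using a random effects Poisson regression analysis, including the following covariates: ward (random effect), institution and the baseline results of the ward". The Discussion repeats the list as the answer to clustering: "Therefore this study will consider the following covariates: ward (random effect), institution and the baseline results of the ward". Only ward is marked as random.

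Study design and setting gives the number of units: "The hospital wards (n = 10) were internal medicine wards (n = 4) and surgical wards (n = 6) from four hospitals", and ten nursing home wards, seven for patients with physical impairments "or rehabilitation wards (n = 3) from six nursing homes". Each setting has five intervention wards. Randomisation was stratified by centre and ward type.

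The sample size was set "with a two-sided alpha of 0.05 and 80% power for the analysis of both the hospital and the nursing homes data". On clustering it says "As randomisation was on ward level, a ward was considered to be a cluster" and "an intra class correlation coefficient of 0.01 was used in the calculation". It asks for 1250 patients per hospital group (12% to 6%) and 100 per nursing home group (60% to 36%). Secondary outcomes are to be handled in a similar way with linear and logistic random effect models.

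**The concern.** The treatment effect is a between-ward contrast, so its precision has to be judged from the variation between wards. Ten wards give little information on that variation, and the institution terms use up much of it. A maximum-likelihood ward variance is biased downwards when many fixed effects are fitted to few clusters, and is often estimated as zero. The model then becomes an ordinary Poisson regression. A z or chi-square test on it ignores the clustering for which the sample size was inflated. At stake are intervals that are too narrow and a false-positive rate above the stated two-sided 0.05 on the primary outcome.

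**Working it through.** **1. The plan's sample size.** Two-proportion formula (pooled variance, no continuity correction) times the design effect 1 + (m - 1) x ICC.
- Hospitals: 356 per group unclustered; m = 1250/5 = 250; design effect 1 + 249 x 0.01 = 3.49; 356 x 3.49 = 1243, against the stated 1250. Reproduced.
- Nursing homes: 67 per group; m = 100/5 = 20; design effect 1.19; 67 x 1.19 = 80 (90 with continuity correction), against the stated 100. Not reproduced, but on the safe side under these formulas.

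**2. Ward-level degrees of freedom, institution fixed.**
- Hospitals: intercept 1 + arm 1 + institution 3 + baseline 1 = 6; 10 - 6 = 4.
- Nursing homes: 1 + 1 + 5 + 1 = 8; 10 - 8 = 2.

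The two-sided 5% critical values of t are 2.78 (4 df) and 4.30 (2 df), against 1.96 for z.

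**3. Why the settings differ.** The squared between-ward coefficient of variation is ICC x p(1 - p)/p². The Poisson part is 1/(expected events per ward). The table shows the true variance relative to the Poisson variance, and the error rate if a z test ignored ward variation entirely (a rough guide, leaving aside covariate adjustment).

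| Setting | Between wards | Within ward | Poisson part | Ratio | Error rate |
|---|---|---|---|---|---|
| Hospitals, 30 events | 0.0733 | 0.0333 | 0.0333 | 3.20 | 27% |
| Nursing homes, 12 events, Poisson | 0.0067 | 0.0833 | 0.0833 | 1.08 | 6% |
| Nursing homes, overdispersed counts | 0.0067 | 0.1333 | 0.0833 | 1.68 | 13% |
| Nursing homes, yes/no outcome | 0.0067 | 0.0333 | 0.0833 | 0.48 | 0.5% |

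The error rate is 2[1 - Φ(1.96/√ratio)]. The overdispersed row takes the variance per patient as mean + mean², so 20 x (0.6 + 0.36)/12² = 0.1333. That is an assumption.

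**4. Simulation under no effect.** Poisson random-intercept model by maximum likelihood with arm, institution, log baseline rate and ward. Assumed: ward layouts 4+2+2+2 and 2+2+2+2+1+1. The sensitivity figures also assume baseline numbers one third of follow-up and half of the ward variance persisting from baseline to follow-up.
- Hospitals, ICC 0.01: Wald z 15-20%, likelihood ratio 17-18%. The ward variance is estimated as about zero in roughly half to three quarters of trials.
- Hospitals, other ICCs (Wald z): 5% at 0, 7% at 0.001, 17% at 0.005, 25% at 0.02-0.05. With 125 patients per ward at ICC 0.01: 14%.
- Hospitals, ICC 0.01, without institution and baseline: Wald 10%, likelihood ratio 8%.
- Hospitals, REML-type fit: 11.2% with z, 4.9% with t on 4 df.
- Nursing homes, ICC 0.01: 5-6% with Poisson counts, under 1% for a yes/no outcome, 8-13% with overdispersed counts. With Poisson counts, 10% at ICC 0.05 and 13% at 0.10. The ward variance is estimated as about zero in 93-100% of trials.

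**5. Ward-level regression with a t reference** (log rate, 0.5 added to counts; ICC 0.01; the plan's own effects).

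| Model | Setting | df | Type I error | Power |
|---|---|---|---|---|
| Arm, institution, baseline | Hospitals | 4 | 5.0% | 60% |
| Arm, institution, baseline | Nursing homes | 2 | 4.5-5.0% | 18-27% |
| Arm, baseline | Hospitals | 7 | 4.9% | 73% |
| Arm, baseline | Nursing homes | 7 | 5.1-5.2% | 48-71% |

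The nursing home ranges run from Poisson counts to a yes/no outcome.

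**The case against.** The article names a model class and covariates, but no estimator, reference distribution or degrees of freedom. It is a condensed account, and a fuller analysis plan may supply them. The published sentence is compatible with a correctly sized test: a REML-type fit with t on 4 df ran at 4.9%. This stands, so the lack of a small-sample method is not in itself an error, and the hospital figure is conditional on the usual default tests. What the article does fix is the covariate list on ten wards. A reference distribution that respects it brings power well below 80%.

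The hospital figure also depends on where the variance lies. If half of it is between hospitals, the institution terms absorb that part and the maximum-likelihood z test runs at about 15%; with 80% between hospitals, about 9%. Still above 5%, but less so.

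Adjusting for institution has a good reason, since centre was a stratification factor. This stands too: dropping it is a trade-off, not a correction. Reading institution as fixed is an inference from ward alone being labelled random.

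A reader might infer that the error rate is well above 5% in both settings. The documents do not support that for nursing homes. Their own ICC, 20 patients per ward and Poisson counts give about 5%. Inflation there needs overdispersed fall counts or a larger ward variance, and the article states neither.

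**Conclusion.** The point holds, mainly for hospitals. At the plan's own ICC and ward size, the specified covariates with maximum likelihood and large-sample tests give a type I error of about 15-20% instead of 5%. It is about 11% with REML-type fitting and z, and lower where variance lies between hospitals. In nursing homes the error rate is about 5% under the stated figures and 8-13% under assumed overdispersion. The ward random effect there gives little protection, because its variance is estimated as about zero in more than 90% of trials.

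In both settings, a test that respects the 4 or 2 residual degrees of freedom does not reach the stated 80% power. These results rest on institution being fixed and on the assumed ward layouts, since the randomisation figure is not shown. The power figures also rest on the assumed baseline size and persistence.

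**What to change.** Test the treatment effect against a t distribution with residual ward-level degrees of freedom. There are two routes:
- A ward-level regression of log follow-up rate on arm and log baseline rate. State a rule for wards with no events, such as adding a small constant. If baseline numbers are a third of 20 per ward, at least one of the ten nursing home wards has no baseline events in about 17% of trials.
- The mixed Poisson model with between-ward degrees of freedom. REML-type fitting is preferable here: maximum likelihood with t on 4 df still ran at about 7% in hospitals, and with t on 2 df it almost never rejected under no effect in nursing homes.

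Decide explicitly whether institution stays as a fixed term, weighing stratification against 4 and 2 degrees of freedom, and restate power for the analysis chosen. Use the same reference for the ward-clustered secondary outcomes.

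The cost is a change of analysis wording, wider intervals (multiplier 2.36 on 7 df, 2.78 on 4, 4.30 on 2, against 1.96) and a less favourable stated power.
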